### 4.4. Outcome Measures

Outcomes will be assessed at 5 timepoints: baseline (Week 0), post-iTBS (Day 5, Week 1), mid-intervention (Week 5), post-intervention (Week 10), and follow-up (Week 18). As this is a feasibility pilot trial, the primary outcomes are feasibility, acceptability, adherence, and safety. The predefined progression (“stop/go”) criteria in Table 1, spanning recruitment, eligibility, adherence, tolerability, acceptability, and retention, will determine whether to proceed to a full-powered definitive trial, while safety is monitored throughout. Each primary domain is operationalised below.

**Feasibility (recruitment and retention).** Recruitment feasibility will be reported descriptively, including the number of participants registering interest, the proportion screened, eligibility yield, and the time taken to reach the target sample; these indicators establish whether recruitment is viable within the study’s eligibility constraints ahead of a definitive trial. Retention will be expressed as the proportion of randomised participants completing the post-iTBS (Week 1), post-intervention (Week 10), and follow-up (Week 18) assessments, and it will be evaluated against the attrition thresholds in Table 1.

**Adherence.** Adherence will be quantified as the proportion of scheduled iTBS and CT sessions completed, against the predefined thresholds in Table 1. iTBS attendance will be verified against site logs, while home-based CT completion will be captured automatically through the online training platform on a per-session basis. Missed sessions and the reasons for non-completion will be documented, and patterns of adherence across the intervention period, including session completion over time, drop-off, and whether adherence differs between the initial in-person sessions and the subsequent home-based period, will be summarised descriptively.

**Acceptability.** Acceptability will be evaluated using a post-intervention satisfaction scale and semi-structured exit interviews examining perceived burden, comfort, and willingness to participate again, and will be judged against the acceptability threshold in Table 1.

**Safety and tolerability.** Safety will be monitored at every iTBS session and throughout the follow-up period; participants will be asked to report adverse sensations (e.g., headache, scalp discomfort, tingling, and fatigue), and all adverse events (AEs) will be reviewed for severity and relatedness and managed in accordance with the safety procedures described in Section 4.10. Tolerability will be operationalised as the proportion of withdrawals that are not attributable to intervention-related AEs, and will be evaluated against the threshold in Table 1.

Secondary outcomes include cognitive measures of verbal memory (CVLT-II), and episodic memory (RBANS Story Recall), executive function and processing speed (D-KEFS TMT; WAIS-IV Coding, Similarities; Digit Span), functional independence (HBA-FAQ), psychological well-being (PHQ-9, GAD-7, PSQI), and health-related quality of life (EQ-5D-5L). All measures were selected based on clinical relevance and psychometric properties (Supplementary Table S1). These outcomes are exploratory and are included not to establish efficacy but to estimate the magnitude and variability of potential change and to inform outcome selection and sample-size estimation for a future definitive trial. Exploratory signals of change will be characterised using effect size estimates (Cohen’s d) with means, standard deviations, and 95% confidence intervals.

Tertiary outcomes are mechanistic and include neurophysiological measures of cortical excitability and inhibition using paired-pulse TMS paradigms, including short- and long-interval intracortical inhibition (SICI, LICI), resting-state EEG and event-related potentials (ERPs) recorded during cognitive tasks. Given the feasibility design, these neurophysiological measures are exploratory and hypothesis-generating. They are intended to determine which markers can be feasibly acquired and are worth retaining as mechanistic outcomes in a definitive trial.

### 4.5. Neurophysiological Recording

Participants will undergo all assessments in a quiet, temperature-controlled room at either site. EEG data will be acquired using the Compumedics Okti^®^ 32-channel portable acquisition system (Compumedics Ltd., Abbotsford, VIC, Australia). Participants will be fitted with the Okti^®^ EEG recording apparatus and electrooculogram (EOG) electrodes and seated approximately 80 cm from a 21-inch monitor. Electrode placement follows the international 10–20 system across 32 channels (Fp1 through Oz, including AFz, FCz, M1 and M2). Signals will be referenced online to Cz, sampled at 1000 Hz, with a DC–70 Hz bandwidth and a 50 Hz notch filter. EOG electrodes will be placed vertically above/below the left eye, and horizontally 1 cm lateral to the outer canthi of each eye.

A brief EOG calibration task will precede EEG recording to facilitate later artefact correction using the Revised Aligned Artefact Average (RAAA) method [36]. Resting-state EEG will be recorded in two continuous 3 min blocks (eyes open/close), following validated protocols for ageing populations [37,38]. Spectral analysis will extract aperiodic (1/f) and periodic components as exploratory measures related to cortical excitability and inhibition [39,40].

Continuous EEG will also be recorded during an auditory Go/NoGo task designed to probe attention and cognitive control [41,42]. The task consists of two blocks of 150 pseudorandomised trials (70% Go, 30% NoGo), using 1000 Hz and 2000 Hz tones (80 ms, 15 ms rise/fall), with a 1250 ms stimulus onset asynchrony. Participants respond as quickly and accurately as possible to Go tones and withhold responses to NoGo tones. EEG data will be pre- and post-processed offline to extract ERPs using the HEADBOX Lab pipeline as published previously [43,44,45]. Temporal principal components analysis will be applied to derive N2 and P3 ERP component amplitudes, markers of inhibitory control and attentional allocation known to be sensitive to cognitive changes in MCI.

TMS assessments will include the determination of RMT. SICI and LICI will be assessed using standardised paired-pulse paradigms to probe intracortical inhibitory processes. The test stimulus will be calibrated to elicit an MEP of approximately 1 mV in amplitude in the FDI muscle of the right hand. For SICI, a 90% RMT conditioning stimulus will precede the test stimulus at ISIs of 2, 3, and 5 ms. For LICI, two suprathreshold pulses at 120% RMT will be delivered at ISIs of 50, 100, and 150 ms [46,47].

### 4.6. Participant Timeline

Following eligibility screening and informed consent, baseline assessments will be completed before randomisation. Baseline cognitive assessments will be completed during Week 0, and baseline EEG and TMS will be conducted on Day 1. Participants will then be randomised 1:1 into one of two groups, with the first active or sham iTBS session delivered immediately following randomisation. The intervention begins in Week 1, with active or sham iTBS delivered over 5 consecutive weekdays (Days 1–5). EEG and TMS will be repeated on Day 5 to evaluate short-term effects.

Participants will then complete 9 weeks of home-based CT (Weeks 2–10), with a mid-intervention EEG/TMS at Week 5. At the end of Week 10, post-intervention assessments will include cognitive testing, EEG, and TMS. At Week 18, all assessments will be repeated to evaluate durability of effects. The overall participant flow is summarised in Figure 2 and the Schedule of Activities in Table 4. A complete visual overview of the study design and schedule is provided in Figure S1 (Supplementary Materials).

### 4.7. Sample Size

As this is a feasibility pilot trial, the sample size was not determined by formal power calculations for hypothesis testing. Sample size determination in pilot studies is typically based on practical considerations, study logistics, and precedent rather than statistical power, with 12 participants per group recommended as a reasonable minimum [48]. Feasibility and pilot trials using iTBS and rTMS in MCI have employed sample sizes ranging from 18 to 38 participants [49]. A sample of 44 participants (22 per group) is consistent with and exceeds these precedents, and is sufficient to characterise feasibility outcomes, estimate variability in cognitive measures, generate preliminary effect size estimates, and is expected to provide preliminary neurophysiological data to inform the design of a future definitive trial. An anticipated dropout rate of ~20% has been accounted for [50], and effect size estimates will build on a pooled effect size of g = 0.36 for CT in MCI [11] to inform a future definitive trial.

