## 4. Methods

### 4.1. Study Design and Setting

This is an 18-week, randomised, double-blind, sham-controlled, parallel-group feasibility pilot trial conducted across two Western Sydney University research sites: NICM Health Research Institute and the School of Health Sciences. The trial comprises two arms: CT + active iTBS and CT + sham iTBS with 1:1 randomisation. Participants will undergo in-person assessments and stimulation sessions during the initial intervention phase, followed by a home-based cognitive training program using a secure, university-hosted online platform developed using the Flask web framework (Python 3.11). Data will be stored securely via REDCap (Vanderbilt University, Nashville, TN, USA), with remote coaching delivered through Zoom Video Communications, Inc. (San Jose, CA, USA) to support adherence. This protocol was developed in accordance with the SPIRIT guidelines and adheres to the CONSORT extension for randomised pilot and feasibility trials, as well as the principles of ICH E6 Good Clinical Practice.

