### 4.12. Statistical Analysis Plan

Consistent with the feasibility objectives of this trial, the primary analysis will focus on descriptive statistics, with feasibility outcomes compared against the predefined thresholds in Table 3 to guide progression to a definitive trial.

Secondary cognitive, functional, and psychological outcomes will be analysed using linear mixed-effects models (LMMs) to account for repeated measures and group differences. Fixed effects will include group (CT + iTBS, CT + sham-iTBS), time (baseline, post-iTBS, mid-intervention, post-intervention, follow-up), and their interaction. Participant ID will be modelled as a random effect. Model assumptions (e.g., normality of residuals, homogeneity of variance) will be tested and corrected as needed. Effect sizes will be estimated using Cohen’s d or f or partial η^2^ with 95% confidence intervals to inform sample size calculations for a future adequately powered trial. Analyses will be conducted using SPSS v25.0 (IBM Corp., IBM Corp., Armonk, NY, USA), Stata (StataCorp, College Station, TX, USA), or R (R Foundation for Statistical Computing, Vienna, Austria). *p*-values will be reported as nominal exploratory statistics and will not be interpreted as confirmatory evidence of efficacy. Covariates (age, sex, education) may be included in sensitivity analyses. Neurophysiological–cognitive correlations will be reported descriptively. Analyses will follow an intention-to-treat principle, with missing data handled using multiple imputation where appropriate.

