## 5. Discussion

This protocol describes a randomised, double-blind, sham-controlled feasibility pilot trial evaluating the combined delivery of iTBS and structured cognitive training in people with MCI. The study is designed to address the gap between preliminary evidence suggesting potential cognitive benefits from CT and neuromodulation and the practical requirements for implementing a combined intervention in a future definitive trial. By prioritising feasibility, acceptability, adherence, and safety, the study will assess whether the intervention can be delivered as planned in the target population and whether predefined progression criteria are met.

A key strength is the integration of a brief iTBS protocol with a structured CT program that transitions from supervised in-person sessions to home-based training, balancing standardisation and participant support with accessibility and real-world feasibility. The inclusion of EEG and TMS measures provides an opportunity to explore neurophysiological changes that may accompany cognitive change, providing insights into biological drivers of treatment responsivity, although these analyses are exploratory and not intended to establish definitive mechanisms.

Several limitations should be considered. First, the feasibility sample is not powered to detect definitive between-group treatment effects; cognitive and neurophysiological findings will therefore be interpreted as preliminary estimates to inform the design and sample size of a future adequately powered trial. Second, eligibility criteria required for participant safety, intervention delivery, and study standardisation may limit generalisability to the broader MCI population; requirements relating to age, English proficiency, handedness, digital access, and TMS eligibility may yield a sample that is healthier or more technologically able than the wider MCI population. Third, the mixed in-person and home-based delivery model may introduce variability in the context in which CT is completed, although online completion will be automatically recorded and adherence patterns monitored. Finally, because the intervention combines iTBS with a structured cognitive training program, psychoeducation, and remote support, any subsequent signals of cognitive change cannot be attributed to a single component.

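### The effect size cited for planning the definitive trial (g = 0.36) is for cognitive training, which both arms receive, and the pilot's own d is too imprecise to set the target instead

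*Protocol article*

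**What the plan says.** Section 4.7 states that "the sample size was not determined by formal power calculations for hypothesis testing". It justifies 44 participants by precedent and then turns to the next trial, for which "effect size estimates will build on a pooled effect size of g = 0.36 for CT in MCI".

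Section 4.1 defines the comparison: "The trial comprises two arms: CT + active iTBS and CT + sham iTBS with 1:1 randomisation". Section 4.3.3 describes a single CT programme, with psychoeducation and coaching, and makes no difference by arm. The mixed model in section 4.12 has group, time and their interaction as fixed effects, and CT is part of both group labels.

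Sizing the definitive trial is a declared purpose of the pilot. Sections 3 and 4.4 and the Discussion say so of the secondary outcomes or the cognitive findings. Section 4.12 plans Cohen's d, f or partial eta-squared "with 95% confidence intervals to inform sample size calculations for a future adequately powered trial". No section says how the external figure and the pilot estimates will be combined, and none gives a numerical effect for active against sham iTBS on top of CT.

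**The concern.** A treatment given identically to both arms drops out of the randomised difference, apart from any interaction with the randomised component. What remains here is the effect of adding active iTBS to CT. A pooled CT effect answers a different question, and the increment could be smaller or larger than it. The Introduction does mention earlier studies of CT plus rTMS against CT alone, which is the nearer comparison, but reports no effect size from them.

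The pilot's own estimate targets the right contrast, but with about 20 participants per arm it is very imprecise. A planner who combines the two, or takes whichever looks more favourable, would size the definitive trial on a number with little bearing on what iTBS adds.

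**Working it through.** **Inputs from the protocol article**
- 22 per group and 44 in total (4.7): "A sample of 44 participants (22 per group) is consistent with and exceeds these precedents".
- Minimum from precedent (4.7): "with 12 participants per group recommended as a reasonable minimum". The earlier trials cited had 18 to 38 participants.
- Dropout (4.7): "An anticipated dropout rate of ~20% has been accounted for".
- External effect: g = 0.36, for CT (4.7).

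**Assumed here, because the article does not state them:** two-sided 5% and 80% power for the definitive trial; SD = 1; increments of 0.20, 0.25, 0.30 and 0.50 for iTBS over CT, for illustration.

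**1. The plan's own figure.** No formula is given for 44, so it cannot be derived, only checked against its stated basis. The minimum of 12 per group, inflated for 20% dropout, is 12 / 0.8 = 15, and 22 exceeds it. 44 also exceeds the cited range of 18 to 38. Expected completers are 22 × 0.8 = 17.6 per group. The figure does not come from g = 0.36: step 3 shows that an effect of that size needs 122 per arm, and 22 per arm would have about 22% power to detect it. That agrees with the statement that the pilot is not powered.

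**2. Precision of the pilot's d.** For an unadjusted two-group comparison, SE(d) = √(2/n + d²/(4n)) with n per arm, and the 95% CI is d ± 1.96 × SE. At d = 0.36:
- n = 22: SE = √(0.0909 + 0.0015) = 0.304; CI 0.36 ± 0.60, which is -0.24 to 0.96.
- n = 18: SE = √(0.1111 + 0.0018) = 0.336; CI 0.36 ± 0.66, which is -0.30 to 1.02.

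The chance that the pilot shows d of at least 0.36, using SE = √(2/n), is about 28% (n = 22) or 30% (n = 18) if the true increment is half that, 0.18. It is about 12% or 14% if the true increment is zero. A pilot estimate that seems to agree with the cited figure would therefore be weak evidence for it.

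The pilot estimates variability much better. With 34 degrees of freedom the 95% CI for an SD runs from about 0.81 to 1.31 times the estimate.

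**3. Consequence for the definitive trial.** Normal approximation: n per arm = 2 × (1.960 + 0.842)² / d² = 15.70 / d². At d = 0.36 this is 15.70 / 0.1296 = 121.1, so 122 per arm. With 122 per arm, power is Φ(d × √(122/2) − 1.96).

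| True increment (assumed) | Needed per arm for 80% power | Power with 122 per arm |
|---|---|---|
| 0.50 | 63 | above 80% |
| 0.36 | 122 | 80% |
| 0.30 | 175 | 65% |
| 0.25 | 252 | 50% |
| 0.20 | 393 | about 34% |

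At 0.50, 122 per arm is nearly twice what is needed. At 0.20 it is less than a third. Taking the pilot's point estimate instead offers no protection: a d of 1.0, inside the interval for 18 completers per arm, would imply only 16 per arm.

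**The case against.** The strongest reply is that nothing has been fixed. The sentence in 4.7 is loose, gives no formula, power or size for the definitive trial, and does not state that trial's comparator. No analysis or progression criterion in this pilot uses an effect size. All of that is true. But the effect sizes planned in 4.12 come from a model with CT in both groups, so a CT effect is not something they can build on.

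A second reply is that imprecision is already disclosed. The article repeatedly calls the findings preliminary, promises 95% confidence intervals, and already plans to estimate variability and retention. This softens the point. The caveats, however, guard against claims of efficacy and leave the stated use for sample size in place.

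Third, the intervals above are unadjusted. The planned mixed model uses all visits, including baseline, and may narrow them somewhat. That stands, and the figures should be read as approximations.

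A reader might also infer three stronger things that the document does not support:
- **That the definitive trial will be under-sized.** This needs an increment below 0.36, which the article neither gives nor rules out. A larger increment, or a low pilot estimate, would push towards over-sizing.
- **That 44 is wrong.** It rests on precedent and not on g = 0.36.
- **That the Discussion is in error where it says** "any subsequent signals of cognitive change cannot be attributed to a single component". On its natural reading the sentence concerns change within participants, and of that it is true. It could only be clearer.

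**Conclusion.** The point holds as a wrongly stated planning basis. The cited g = 0.36 belongs to a component common to both arms and does not estimate the randomised contrast, for which the article gives no figure. The pilot's d cannot fill the gap, with an unadjusted 95% CI half-width of about 0.60 to 0.66. The effect on the definitive trial can go either way, and its size depends on an unknown increment: the power of 65%, 50% or 34% for a 122-per-arm trial rests on assumed increments of 0.30, 0.25 and 0.20, and on an assumed 80% power and two-sided 5%. Nothing in the conduct or size of this pilot is affected. The wording should be changed, because informing the next trial's sample size is a declared purpose of this one.

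**What to change.** - **Section 4.7:** remove g = 0.36 as a basis for the definitive trial's target difference, or label it as a CT effect that does not apply to this contrast. State that the randomised contrast is the effect of adding active iTBS to CT.
- **Section 4.12:** say that the pilot will supply the SD, the within-person correlation and attrition for the definitive sample size; that the target difference will be a justified important difference for the iTBS increment; and that the pilot's between-arm confidence interval will only check whether that target remains plausible.
- **Discussion (optional):** clarify that the limit on attribution concerns change within an arm, while the between-arm difference reflects iTBS given in the presence of CT.

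The cost is a few sentences. Sample size, data collection and the planned models stay as they are, so the change can be made while recruitment continues. The important difference itself can be set later, before the definitive trial is designed.

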### 4.9. Randomisation and Blinding

Randomisation will be implemented using REDCap with a 1:1 allocation ratio. Stratified block randomisation (block of 4 and 6) will be used, stratified by sex due to known sex differences in cognitive ageing and TMS responsiveness. The allocation sequence is computer-generated by an independent staff member and uploaded to REDCap, concealed until post-baseline assessments. Participants, outcome assessors, and data analysts will be blinded. Only the laboratory technician responsible for stimulation setup will access the allocation, solely to deliver the assigned active or sham stimulation, and will not be involved in outcome assessment or data analysis. Participants will be asked not to share their experience with others, to maintain blinding.

### 4.10. Safety

Adverse events will be monitored from first intervention to final follow-up. Serious AEs (SAEs) will be classified per NHMRC and ICH guidelines. Common iTBS side effects (e.g., headache, scalp discomfort) will be monitored. Though seizures are rare (~0.02%) [25], procedures are in place, including cessation of stimulation, and emergency medical response if required. SAEs will be reported to the Western Sydney University HREC within 24 h, with REDCap alerting the study physician automatically. Participants will be followed until AEs/SAEs resolve or stabilise. Unblinding may occur if necessary. AEs/SAEs will be summarised in annual safety reports.

### 4.11. Data Management and Monitoring

Study data will be collected using REDCap in real time. Participants will be assigned unique IDs, with identifiable information stored separately with password protection and encryption. Access will be role-restricted with audit trails. Data will be stored securely on Western Sydney University’s network and retained for 15 years post publication. Upon completion of the trial, the de-identified dataset generated during the study may be archived and will be made available from the corresponding author upon reasonable request, subject to ethical and privacy requirements. The research team will permit audits and regulatory review as required.

